## Abstract

**Background:**

Self-management has become increasingly popular in the management of chronic diseases. There are many different self-management models. Meta analyses of arthritis self-management have concluded that it is difficult to recommend any one program in preference to another due to inconsistencies in the study designs used to evaluate different programs.

The Stanford Arthritis Self-Management Program (ASMP), most commonly delivered by trained lay leaders, is a generic program widely used for people with rheumatological disorders. We have developed a more specific program expressly for people with osteoarthritis of the knee (OAKP). It includes information designed to be delivered by health professionals and results in improvements in pain, function and quality of life.

*Aim: *To determine whether, for people with osteoarthritis (OA) of the knee, the OAKP implemented in a primary health care setting can achieve and maintain clinically meaningful improvements in more participants than ASMP delivered in the same environment.

**Methods/Design:**

The effectiveness of the programs will be compared in a single-blind randomized study.

*Participants: *146 participants with established OA knee will be recruited. Volunteers with coexistent inflammatory joint disease or serious co-morbidities will be excluded.

*Interventions*: Participants will be randomised into either OAKP or ASMP groups and followed for 6 months.

*Measurements*: Assessments will be immediately before and after the intervention and at 6 months. Primary outcome measures will be WOMAC and SF-36 questionnaires and a VAS for pain. Secondary outcomes will include balance, tested using a timed single leg balance test and a timed step test and self-efficacy. Data will be analysed using repeated measures ANOVA.

**Discussion:**

With an aging population the health care costs for people with arthritis are ever increasing. Although cost analysis is beyond the scope of this study, it is reasonable to expect that costs will be greater when health professionals deliver self-management programs as opposed to lay leaders. Consequently it is critical to examine the relative effectiveness of the primary care management strategies available for OA.

**Trial Registration:**

This study is registered with the Australian New Zealand Clinical Trials Registry: 12607000031460

## Background

Chronic disease is a major concern with an ageing population, and arthritis is one of the most prevalent chronic diseases affecting 16.7% of the population in Australia [1]. Osteoarthritis is the most common form of arthritis affecting 25% of the population over the age of 65 years. The joint most frequently affected is the knee [2].

Self-management interventions are becoming increasingly popular for many chronic diseases, however the length of program and mode of delivery varies greatly between programs and between illnesses [3]. The programs may utilise a combination of health professionals (physiotherapists, occupational therapists, nurses and dieticians), trained health educators, mental health workers, and occasionally physicians, for program delivery. Other programs have lay leaders who usually deliver a scripted program. The mode of delivery also varies greatly from face to face to audiotape; group or individual contact and more recently internet based programs [4].

Comparing different self-management models is difficult as the needs of people with chronic diseases differ according to their illness. Asthma and diabetes self-management programs emphasise medication delivery and compliance, whereas self-management for other conditions may focus more on pain management strategies. Even within the broad category of arthritis, the self-management needs of people with different types of arthritis such as rheumatoid arthritis or osteoarthritis are not the same.

One widely utilised arthritis self-management program is the Stanford University's Arthritis Self Management Progam (ASMP), which is delivered by trained lay leaders [5]. The ASMP has been tested widely. The majority of studies have been conducted in the USA or UK. Many, but not all of these studies report program efficacy. Systematic reviews of self-management interventions that include the ASMP have shown there is a trend towards a small benefit for people with arthritis, but the results were not statistically significant and there was a suggestion of publication bias [3,6,7]. At this stage, it is not possible to unequivically claim that ASMP is effective.

In view of the high prevalence of osteoarthritis of the knee and the absence of unequivocal evidence of effectiveness of ASMP, we developed an education self-management program specifically for people with osteoarthritis of the knee (OAKP). The program is delivered by health professionals with information and instruction that utilises their knowledge and skills within a self-management construct. The OAKP has been tested in a quality assurance project [8] and a randomised controlled trial (RCT) the results of which show improvements in quality of life, pain and function compared to a control group [9].

With an aging population the costs associated with arthritis are ever increasing [1]. Although cost analysis is beyond the scope of this study, it is reasonable to expect that costs will be greater when health professionals deliver self-management programs as opposed to lay leaders. Therefore it is important to establish whether delivery by health professionals results in added benefits and/or improvements in outcomes. At present both ASMP and OAKP are offered as clinical services at Arthritis WA.

Accordingly, we propose to conduct a RCT to examine the differences between OAKP, directed and delivered by health professionals, and ASMP, delivered by trained lay leaders.

### Aims

To compare the effectiveness of the OAKP and ASMP for people with OA knee.

### Hypothesis

A greater proportion of people with osteoarthritis of the knee that complete the OAKP will report clinically meaningful improvements in pain, knee function and quality of life, at 8 weeks, and 6 months compared to those who complete the ASMP.

## Methods/Design

### Study Design

A two-group single blind, randomised, repeated measure study design will be used to compare the programs (Figure 1). Participants in both groups will continue to receive standard medical management as required.

**Figure 1 F1:**
[figure not shown]
**Study Design Flow Chart**.

### Group allocation

To ensure manageable numbers for intervention groups, participants will be randomised in blocks. Pre-prepared cards indicating group assignment will be placed in sealed opaque envelopes and drawn as a lottery by a third party for allocation to treatment groups. Allocation will not take place until a whole block has been recruited in order to ensure optimum group sizes. This method of randomisation worked successfully for a previous OAKP RCT [10].

### Subjects

As this study will evaluate a clinical service currently provided by Arthritis WA, the study recruitment strategies and selection criteria have been selected to operate within that context. The participants will be men and women with established OA of one or both knees. The operational definition for OA knee used for the OAKP is OA of the knee diagnosed either by clinical examination or by radiological (X-Ray) evidence. The participant will be required to have a referral and a definitive diagnosis of OA made by a family physician/general medical practitioner or specialist physician in order to be eligible to participate in the study. In addition, the American Rheumatology Association clinical classification algorithm will be applied. The overall sensitivity and specificity of this method are 89% and 88% respectively [11]. The inclusion criteria for determining suitability have previously been used for a quality assurance study and a randomised RCT [8,10] and in both it was found to work well. Participants will not be excluded on the basis of severity of symptoms. They will be required to be ≥ 18 years of age, English speaking and to provide consent to randomisation as demonstrated by signed written authority. Participants with rheumatoid arthritis or other inflammatory joint disease, serious co-morbidities, those who plan to have knee surgery within 6 months of commencing the study or who have physical impairments that preclude fulfilment of the requirements of either program will be excluded (Additional file 1).

Recruitment strategies will include active promotion to general practitioners, rheumatologists and health professionals through professional societies. The study will also be offered to those people with osteoarthritis of the knee who make general inquiries to Arthritis WA, and to the general public through advertising and media coverage.

#### Interventions

Both programs will be delivered over a six-week period with participants attending one session of two and a half hours per week. To facilitate optimum group dynamics, the target size for each group will be 12 participants, although this may vary as a result of recruitment and randomisation.

There will be a pool of 4 group leaders for each program, health professionals for OAKP and lay leaders for ASMP. The health professionals will be trained in delivery of self-management programs and the lay leaders will be experienced ASMP facilitators who have completed the "Train the Trainer course" conducted at Arthritis WA, under licence from Stanford University. Facilitators will work in pairs when delivering the programs.

The fidelity of OAKP and ASMP will be maintained as both programs have manuals for course delivery.

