### Statistical Power

Power calculations are based on the achievement of a minimal clinically meaningful improvement [24]. With an alpha (1-tailed) of 0.05 and a sample size of 73 people in each group, this study will have power of 80% to show that the response rate for ASMP is at least as high as the response rate for OAKP. This assumes that the response rates for the ASMP and OAKP groups are equal (at 38.0%, the level of response achieved for the WOMAC function scale in our earlier RCT [10]), and that a difference of 20.0 points or less is unimportant and allows for 20% drop out.

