### Data Analysis

Data will be analysed in a blinded manner using SPSS v17 for Macintosh. Treatment groups will be examined for comparability at baseline using unpaired t-tests or Chi-squared test as appropriate. Main comparisons between treatment groups will be performed using an intention to treat analysis. For all subjects who complete the 6-month measurements, previous values will be carried forward to replace any interim missing values.

The proportion of participants achieving minimal clinically meaningful improvement in the health status, quality of life and pain will be computed for each group at each observation time. The effect of the treatment, in terms of the proportion showing minimal clinically meaningful improvement will be examined using Chi-square test. Separate analysis will be conducted for each of the outcome variables of interest.

Further, participants will be classified as overall responders or non-responders. A favourable response to treatment (responder) will be defined according to scenario D of the OMERACT-OARSI criteria [25]. That is, an improvement of ≥ 50% in pain or function and an absolute change of ≥ 20 points on a 100 point scale, OR an improvement of at least 2 of the following: An improvement of ≥ 20% and an absolute change of ≥ 10 in two of pain, function and global health. The proportion of participants achieving responder criteria will be computed for each group at each observation time. The effect of the treatment, in terms of the proportion of responders will be examined using Chi-square test.

Finally, repeated measures ANOVA will be used to examine the differences between groups over time. Statistical significance will be inferred at a 1-tailed p < 0.05. Results will not be adjusted for multiple comparisons as all outcomes of interest have been nominated a priori and such adjustment would likely render all findings of interest non-significant, despite their clinical importance [26]. Separate analysis will be conducted for each of the outcome variables of interest.

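### Participants are taught in classes, but the planned tests and the power figure treat them as independent; if outcomes within a class are correlated, both are too optimistic

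*Protocol article*

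**What the plan says.** All places are in the Protocol article.

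- **Group allocation:** individual participants are randomised in blocks, and allocation waits until a whole block has been recruited so that class sizes are suitable.
- **Interventions:** both programs run for six weeks with one session of two and a half hours a week. For reasons of group dynamics, "the target size for each group will be 12 participants", although this may vary. "There will be a pool of 4 group leaders for each program", and they teach in pairs. Both programs have delivery manuals.
- **Statistical Power:** "With an alpha (1-tailed) of 0.05 and a sample size of 73 people in each group", "this study will have power of 80" per cent. Response is assumed equal in the two arms ("at 38.0%, the level of response achieved for the WOMAC function scale"), the margin is 20 points, and 20% drop-out is said to be allowed for.
- **Data Analysis:** "The effect of the treatment, in terms of the proportion of responders will be examined using Chi-square test", and the proportions with minimal clinically meaningful improvement are tested in the same way. Then "repeated measures ANOVA will be used to examine the differences between groups over time". "Statistical significance will be inferred at a 1-tailed p < 0.05".

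Neither the power statement nor the analysis section mentions class, leader, an ICC or a design effect.

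**The concern.** Each class lies wholly within one program. Classmates share discussion, timing and a pair of leaders, and the article itself expects the way a group works together to matter. Randomising individuals does not remove correlation that arises after allocation from being taught together. A chi-square test on participants takes no account of it. Repeated measures ANOVA deals with correlation between measurements on the same person, not between people in the same class.

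Two things are at stake. A difference between a few classes or leader pairs could be read as a difference between programs. And the trial may have less power than stated to support a conclusion about whether delivery by health professionals adds benefit.

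**Working it through.** **Inputs from the article.** Response 38% in both arms, margin 0.20, one-sided alpha 0.05, power 80%, 73 per arm, drop-out 20% (Statistical Power); class size 12 (Interventions).

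**Input not in the article.** The ICC of the outcome within a class, counting only correlation that arises after allocation. It is assumed here at 0.01, 0.02, 0.05 and 0.10.

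**Step 1: reproduce the plan's figure.**
n per arm = (1.645 + 0.842)² × 2 × 0.38 × 0.62 / 0.20² = 72.8, rounded up to 73.
Standard error with 73 per arm = √(2 × 0.38 × 0.62 / 73) = 0.0803.
Power = Φ(0.20/0.0803 − 1.645) = 80.1%.
The match is exact with independent participants, that is, with a design effect of 1. No allowance for clustering is hidden in the 73.

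**Step 2: number of classes.** 73/12 = 6.1, so about six per arm and 12 in all.

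**Step 3: design effect.** DE = 1 + (12 − 1) × ICC.

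**Step 4: true one-sided error of the unadjusted 5% test.** 1 − Φ(1.645/√DE).

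**Step 5: power with 73 evaluable per arm.** Φ(0.20/(0.0803 × √DE) − 1.645).

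| Assumed ICC | DE | True one-sided error | Power, 73 evaluable per arm |
|---|---|---|---|
| 0 | 1.00 | 5.0% | 80% |
| 0.01 | 1.11 | 5.9% | 76% |
| 0.02 | 1.22 | 6.8% | 73% |
| 0.05 | 1.55 | 9.3% | 64% |
| 0.10 | 2.10 | 12.8% | 53% |

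Example at ICC 0.05: √1.55 = 1.245; 1.645/1.245 = 1.321, which leaves 9.3% in the tail; 0.20/(0.0803 × 1.245) − 1.645 = 0.355, which gives 64%.

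A simulation of the participant-level test (beta-binomial response of 38%, six classes of 12 per arm, 200,000 runs) gave one-sided errors of 6.1%, 7.0%, 9.6% and 13.3% for the four ICCs, against 5.1% with no clustering. The formula therefore does not exaggerate.

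**Step 6: few classes.** With about 12 classes, a class-based analysis has about 12 − 2 = 10 degrees of freedom. The one-sided critical value rises from 1.645 to 1.812, a ratio of 1.102. Intervals widen by √DE × 1.102: 1.054 × 1.102 = 1.16 at ICC 0.01 and 1.245 × 1.102 = 1.37 at ICC 0.05. The powers in the table use the normal critical value and so are somewhat optimistic.

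**Step 7: keep drop-out apart.** The 73 is the number before drop-out. With 20% lost, 73 × 0.8 is about 58 evaluable per arm, and power is Φ(0.20/√(2 × 0.38 × 0.62/58) − 1.645) = 72% with no clustering at all. With both effects at ICC 0.05 (class size 9.6 after losses, DE = 1 + 8.6 × 0.05 = 1.43), power is about 58%. Of the fall from 80% to 58%, drop-out accounts for the step from 80% to 72%, and clustering for the step from 72% to 58%.

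**The case against.** The strongest reply is that the harm is conditional. A reader might infer that the p-values are too small and that the 5% error rate is exceeded. The article does not support that as fact: it requires a positive ICC, and none is given. At ICC 0.01 the error is 5.9% and the power 76%, which is a small loss, and nothing in the article favours 0.05 or 0.10 over 0.01. This stands, and the point is worded accordingly.

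Delivery manuals, and leaders drawn from a pool and working in pairs, may limit variation between classes. This stands in part: manuals can narrow differences between leaders but do not remove the influence of classmates on one another.

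Participants are also randomised within blocks recruited together, so differences between recruitment periods are largely shared by the two arms and tend to cancel. This stands too. It is why the ICC above must mean post-allocation correlation only; an ICC that included period effects would overstate the inflation.

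A reader might also blame clustering for a power below 60%. That combines it with the missing drop-out allowance, which is a separate error. Further, the power statement is framed as ASMP being no worse than OAKP, whereas the Hypothesis section expects OAKP to do better. That mismatch needs its own repair, but clustering affects either framing.

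One defence does not stand: that this is detail left to an unseen analysis plan or full protocol. The article itself names the tests and the sample size, and both rest on independence.

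**Conclusion.** The point holds in conditional form. The plan fixes tests and a power figure that ignore class membership, although treatment is delivered in about six classes per arm. For any positive within-class correlation the direction is certain: standard errors for the program difference are too small and the stated power is too high. The size cannot be fixed from the article. Under assumed ICCs of 0.01 to 0.10 and classes of 12, the one-sided error is about 5.9% to 12.8% and power with 73 evaluable per arm is about 76% to 53%, before the further loss from few degrees of freedom.

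The small leader pool could add to this, but the article does not say whether pairs are fixed or how many classes each pair teaches, so no size can be given for that part. Severity: should be fixed. Confidence is high on the direction and low on the magnitude.

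**What to change.** 1. Record class and leader pair for every participant.
2. Make the main between-program tests account for class with a small-sample method. The sturdier choice with about six classes per arm is a class-level comparison of response proportions and mean changes. The alternative is a mixed model with a random intercept for class and small-sample degrees of freedom; its logistic form is fragile with so few classes. Prespecify the choice instead of testing for clustering first, because the ICC will be poorly estimated.
3. Add a sensitivity analysis for leader pair.
4. Restate power over an assumed ICC range such as 0.01 to 0.10, using 1 + (12 − 1) × ICC, without enrolling more participants. Correct the drop-out allowance as a separate item.

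**Cost.** Two identifier variables and revised wording in the Statistical Power and Data Analysis sections; randomisation and delivery do not change. Intervals become noticeably wider, by about 16% at ICC 0.01 and 37% at ICC 0.05 allowing for about 10 degrees of freedom, and the stated power falls. Restoring 80% power would need about 73 × 1.55 = 113.2, so 114 evaluable per arm at ICC 0.05; that is not proposed here, and the lower power should simply be stated.

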##### OAKP

The health professionals delivering the OAKP will be required to have the knowledge and skills to present information on disease specific topics, exercise advice, and to accurately respond to complex questions.

The Program includes the following aspects of care:

• Osteoarthritis - explanation and implications

• Pain management strategies (cognitive and pharmacological)

• Fitness and exercise (strength, flexibility, aerobic and balance)

• Joint protection

• Nutrition and weight control

• Medication (type, interactions, current trends)

• Correct use of analgesia (use of, therapeutic dosing, types of analgesia, side effects)

• Balance, proprioception and falls prevention,

• Coping with negative emotions

• Self-management skills (SMART goals [**S**pecific, **M**easurable, **A**chievable, **R**ealistic, **T**ime-framed], problem solving, modelling, positive thinking, improving self-efficacy).

##### ASMP

As the ASMP was designed to be delivered by lay leaders to people with a variety of musculoskeletal conditions such as rheumatoid arthritis, osteoarthritis, fibromyalgia and systemic lupus erythematosus, the course content is more generic.

Subjects covered in ASMP include [12]:

• Techniques to deal with problems such as pain, fatigue, frustration and isolation,

• Appropriate exercise for maintaining and improving strength, flexibility, and endurance,

• Appropriate use of medications,

• Communicating effectively with family, friends and health professionals,

• Healthy eating,

• Making informed treatment decisions,

• Disease related problem solving

• Getting a good night's sleep.

### Ethical Issues

This study has been approved by the Human Research Ethics Committee at Curtin University of Technology and meets with CONSORT guidelines. It is registered with the Australian New Zealand Clinical Trials Registry, number: 12607000031460.

All participants will provide written informed consent prior to randomisation. Data access and storage will be in keeping with National Health and Medical Research Council guidelines. License agreements have been obtained for SF-36 and WOMAC Questionnaires.

### Instruments & Assessments

#### Baseline Screening/Assessment

Telephone screening will be conducted with people who enquire to enrol into the study. Suitable candidates will have study information sent to them. Following enrolment and written consent, participants will be randomised into groups. At the baseline assessment, demographic information will be collected including: past medical history, current medications including prescribed, over the counter and natural therapies. Records of medical practitioner referral, diagnosis and X-Ray reports will be collected.

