#### Response to Intervention

Participants will be assessed using the following outcome measures at baseline (Week 1), immediately post-intervention (Week 8), and at 6 months after commencing the program. In addition, VAS pain will be assessed on a week-to-week basis during the first 8 weeks- that is the two assessment weeks and the 6 intervention weeks. A research assistant who will remain blind to group allocation will perform all assessments at all time-points. The primary outcomes for the study will be health status, quality of life and pain severity.

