### Outcome measures

#### Western Ontario and McMaster Universities (WOMAC) Osteoarthritis index

WOMAC measures health status and assesses pain, stiffness and physical function in patients with OA of the hip or knee. For the purpose of this study the Likert (WOMAC LK3.0) format will be used. The WOMAC questionnaire is self-administered and can be completed in less than 10 minutes. Two major validity studies have shown WOMAC pain, stiffness and physical function subscales are valid and that the questionnaire is reliable and sensitive enough to detect changes in health status following a variety of interventions [13,14].

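### As described, randomisation precedes the baseline assessment and nothing keeps participants unaware of their group until the self-completed baseline scores are in, so knowledge of allocation could shift baseline by arm

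*Protocol article*

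**What the plan says.** The Baseline Screening/Assessment section of the protocol article runs through telephone screening, posting of study information, enrolment and consent, and then states: "Following enrolment and written consent, participants will be randomised into groups. At the baseline assessment, demographic information will be collected".

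Other sections fix related points without changing that order:

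- Group allocation: "Allocation will not take place until a whole block has been recruited". It does not say that baseline is measured during this wait, or when participants learn the result of the draw.
- Response to Intervention places the baseline outcome measures in Week 1. The first eight weeks consist of two assessment weeks and six intervention weeks. The abstract likewise puts the first assessment just before the intervention. Neither places it before allocation.
- Study Design calls the trial single blind. Response to Intervention describes one blinded party, the research assistant who does the assessments.
- On the main instrument: "The WOMAC questionnaire is self-administered and can be completed in less than 10 minutes". The SF-36 is also self-administered, and participants mark the VAS themselves.
- Data Analysis defines response by improvement, with both percentage and absolute change required under the overall responder criteria, and adds a repeated measures ANOVA.

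**The concern.** A baseline taken after participants know their group is no longer a purely pre-randomisation measurement. The two arms are easy to tell apart: health professionals with knee-specific content, or lay leaders with a generic course. Someone pleased or disappointed by the draw may rate pain, function or quality of life differently in Week 1. A blinded assessor cannot prevent this, because the assessor does not produce these scores.

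Baseline enters every response definition. It sets the absolute change and is the denominator of the percentage change, and it is also a time point in the ANOVA. A shift at baseline in one arm would therefore appear as a difference in improvement, even if the programmes worked equally well.

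There is a second route. A participant who withdraws on hearing the allocation, before Week 1, has no baseline. No improvement can be calculated for that person. The carry-forward rule in Data Analysis does not help, because it covers only interim gaps in people who complete the 6-month measurements.

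**Working it through.** **Order of steps.** The plan gives no figure on this point, so the main check is to set the sections side by side.

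| Section | What it fixes | Baseline before allocation? |
|---|---|---|
| Baseline Screening/Assessment | Consent, then randomisation, then the baseline assessment | No, the reverse |
| Group allocation | The draw waits for a full block | Silent |
| Response to Intervention | Baseline in Week 1, ahead of six intervention weeks | Silent; places it before the intervention only |
| Abstract, Methods/Design | First assessment just before the intervention | Silent, as above |
| Study Design | Single blind | Silent; no participant blinding described |

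One section orders the two steps, and it puts randomisation first. No section withholds the allocation until baseline is done.

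**Illustration of size.** Inputs from Statistical Power are a 38% response rate in both groups, 73 per group and a one-sided alpha of 0.05. The document gives neither an SD of change nor a likely shift. The following are therefore assumptions: response is a threshold on a normally distributed change score, the true rate is 38% in both arms, and knowledge of allocation makes baseline worse in one arm only, by d SD of change, with follow-up unaffected.

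1. Threshold: 1 − Φ(c) = 0.38 gives c = 0.305.
2. Shifted rate: p(d) = 1 − Φ(c − d). For d = 0.1, 1 − Φ(0.205) = 0.419. For d = 0.2, 1 − Φ(0.105) = 0.458.
3. Chance of a false one-sided result in the direction of the shift: Φ[(δ − 1.645·SE0)/SE1], where δ = p(d) − 0.38, SE0 uses the pooled rate and SE1 the separate rates.
   - d = 0.1: pooled rate 0.3995, SE0 = √(2 × 0.3995 × 0.6005/73) = 0.0811, SE1 = √[(0.38 × 0.62 + 0.419 × 0.581)/73] = 0.0810. Φ[(0.039 − 0.1334)/0.0810] is about 0.12.
   - d = 0.2: pooled rate 0.419, SE0 = 0.0817, SE1 = 0.0814. Φ[(0.078 − 0.1343)/0.0814] is about 0.24.

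| Assumed shift (SD of change) | Response rate in shifted arm | False one-sided result, 73 per group | Same, 58 per group |
|---|---|---|---|
| 0 | 38.0% | 5% | 5% |
| 0.05 | 39.9% | 8% | 8% |
| 0.1 | 41.9% | 12% | 11% |
| 0.2 | 45.8% | 24% | 21% |
| 0.3 | 49.8% | 42% | 36% |

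The 58 is 73 × 0.80, the number left after the stated 20% drop-out if that loss comes out of the 73. For scale, a one-sided 5% result with 73 per group needs a difference of about 1.645 × √(2 × 0.38 × 0.62/73) = 0.132, or 13 percentage points.

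**The case against.** The strongest reply is that the harm depends on disclosure, and the article does not say when participants are told their group. They need to know it by the first class, but Week 1 is an assessment week with no class, and a third party draws the envelopes. The order itself rests on two adjacent sentences, and the flow chart in Figure 1, which might settle it, is not available here. These points stand as limits on certainty. They do not remove the concern, because the only order given is the weaker one and no safeguard is described.

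The illustration can also be challenged. Both arms receive an active programme of equal length, so there is no untreated group to be disappointed, and a reaction that lasted to follow-up would partly cancel in the change score. That is fair, and it is why the table cannot be read as a forecast. Follow-up ratings will be unblinded under any order, so a reordering removes only part of the self-report risk. The planned baseline comparisons might reveal a large shift, but they could neither tell it from chance imbalance nor correct it.

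A reader might also infer that eligibility is verified only after allocation, since the same section ends with: "Records of medical practitioner referral, diagnosis and X-Ray reports will be collected". The document does not support that. The sentence carries no timing, telephone screening comes first, and the Subjects section makes these conditions of entry: "The participant will be required to have a referral and a definitive diagnosis of OA". Nothing provides for exclusion after randomisation, and the main comparisons are by intention to treat.

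**Conclusion.** The concern holds in a limited form. As written, randomisation precedes the baseline assessment, the primary measures are self-completed, and nothing keeps participants unaware of their group until those measures are done. This leaves the improvement-based response rates and the repeated measures ANOVA open to a baseline shift by arm and to withdrawals before baseline.

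That participants do know their group by Week 1 is an inference from the single-blind design; the article does not state it. It would go too far to say that bias will occur, or in which direction. The movement from 38% to about 42% or 46% depends wholly on an assumed shift of 0.1 or 0.2 SD in one arm and on the normal-threshold simplification. It would also go too far to say that no analysis could avoid the problem: a comparison of follow-up scores alone would not use the shifted baseline, but the analyses described are built on change and on repeated measures that include baseline. The point deserves correction before recruitment because the safeguard is cheap, with moderate confidence given the missing flow chart.

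**What to change.** Rewrite the Baseline Screening/Assessment section so that all baseline outcome measures (questionnaires, VAS and performance tests) are completed after consent and before the block's envelopes are drawn. The wait for a full block, described under Group allocation, already provides the interval. If that cannot be scheduled, state that participants are not told their group until their baseline is complete. If either is already the practice, correct the text and check that Figure 1 agrees.

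The cost is mainly scheduling: the whole block must be assessed before the draw, and baseline falls slightly earlier relative to the first class. The lighter option avoids the first of these, but relies on the allocation being kept from participants between the draw and Week 1.
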